
### Measures and procedures

After written informed consent is obtained, parents will fill out an application package which contains questionnaires of demographic and background information such as previous care and medication use. The measurements of academic performance and neurocognitive functioning (primary outcomes) are administered in a child face-to-face meeting which takes place at three consecutive moments: at baseline, directly after treatment and 6 months after treatment. The test battery that will measure academic performance consists of an automated math [15], a spelling skill test [16] and technical literacy [17] test. The neurocognitive functioning test battery consists of tests that measure attention [18], verbal [19,20] and spatial working memory [21], inhibition [20], planning and goal-directed behaviour [22]. Also, both parents and teachers fill out the ‘The Behaviour Rating of Executive Functions’ [23] questionnaire. The secondary outcome measures of this study are behaviour in class, behaviour problems and quality of life of the children. This will also be measured at the three consecutive moments mentioned above. Behaviour in class will be reported by the teacher using the ‘Leervoorwaardentest’, a questionnaire [24]. Both teacher and parents will rate behaviour problems using ‘The Child Behavior Checklist for Ages 6–18 [25] and ‘Teacher’s Report Form for Ages 6-18’ [26]. Before training is started, the Diagnostic Interview Schedule for Children [27] and Social Communication Questionnaire [28] is administered to parents to rule out other behavioural problems or psychiatric problems that meet exclusion criteria. Finally, quality of life is measured by using the Kidscreen-27 [29] questionnaire and is completed by parents and the child. All tests and questionnaires have been selected based on results from a small pilot study and clinical experience. Most of the tests and questionnaires are in line with other relevant international literature. Other aspects that were taken into account were duration of administration, variety of neurocognitive tests that can establish possible near and far transfer effects and methodological points such as presence of Dutch norms and test-retest reliability. Table 1 gives an overview of all the assessments and outcome measures.

**Table 1 T1:** Outcomes measures

	**Measure**	**Informant**	T1	T2	T3
*Primary outcomes*	*Creature counting:* subtest of Test of Everyday Attention for Children [18], measures attentional control and switching	child	*	*	*
	*Score!:* subtest of Test of Everyday Attention for Children [18], measures sustained attention	child	*	*	*
	*Digit span:* subtest of Wechsler Intelligence Scale for Children-III [19], measures verbal working memory	child	*	*	*
	*Span board:* subtest of Wechsler Non Verbal [21], measures visual working memory	child	*	*	*
	*Word list interference:* subtest from Nepsy-II-nl [20], this subtest is designed to asses verbal working memory, repetition and word recall following interference.	child	*	*	*
	*Six part test:* subtest from Behavioural Assessment of the Dysexecutive Syndrome for Children [22], measures planning, task scheduling and performance monitoring	child	*	*	*
	*Inhibition:* subtest from nepsy-II-nl [20], measures the ability to inhibit automatic responses in favor of novel responses and the ability to switch between respons types.	child	*	*	*
	*Behaviour Rating of Executive Functions (BRIEF):* 70 item questionnaire designed to assess executive functioning in the home and school environments [23]	parent/teacher	*	*	*
	*Dictation (PI dictee,* 16): measures spelling skills	child	*	*	*
	*Automated math (Tempo Test Automatiseren,*15): measures degree of automation of addition, subtraction, multiplication and division.	child	*	*	*
	*Speed reading (Een Minuut Test,* 17): measures technical literacy	child	*	*	*
	*Comprehension of instruction:* subtest from nepsy-II-nl [20], measures the ability to receive, process and execute oral instructions of increasing syntactic complexity.	child	*	*	*
*Secondary outcomes*	*Learning conditions test* (Leervoorwaarden test, 24): 70 item questionnaire that measures directly and indirectly learning conditions as concentration, motivation, work rate, task orientation, working according to a plan, persistency, social position in class and relationship with peers and teacher.	teacher	*	*	*
	*Child Behavior Checklist for Ages 6–18 (CBCL/6-18, 25*): 113 item questionnaire designed to measure behaviour problems.	parent	*	*	*
	*Teacher’s Report Form for Ages 6–18 (TRF,* 26): 113 item questionnaire designed to measure behaviour problems.	teacher	*	*	*
	*I-DISC-IV (Diagnostic Interview Schedule for Children,* 27): structured diagnostic telephonic interview, registered via the internet. Measures presence of symptoms and criteria variables as defined by the DSM-IV [14]. Only the domains ADHD, ODD and CD are administered.	parent	*		
	*Social Communication Questionnaire (SCQ, 28*): is a quick screening questionnaire of 40 items for autism spectrum disorders.	parent	*		
	*Kidscreen 27*[29]: 27 item questionnaire that measures quality of life with the dimensions physical well-being, psychological well-being, autonomy & parents, peers & social support and school environment.	child/parent	*	*	*
Intelligence Quotient **	*Shortened version of Wechsler Intelligence Scale for Children**III*[19]*:* subtest Similarities, Block Design, Vocabulary and Information which gives an estimation of the Total IQ	child	*		

T1 = baseline T2 = directly after treatment T3 = follow up after 6 months.

** Intelligence Quotient is only administered if IQ data are not available or when an IQ test has been administered more than two years ago.

### Sample size

For the randomised controlled trial in the first study with two trial arms, 50 children in each trial arm, an effect size of 0.60 can statistically be demonstrated (P < 0.05, 80% power) for comparison of the primary outcome measures of both interventions. This corresponds with an expected clinically relevant difference of 3 points and a standard deviation of 5 on the subtest Digit span from the WISC-III.

For the second study we developed a risk score for the non-responders of the ‘Paying attention in class’ intervention. We expect that 35% (n = 61) of the 175 included children will show no or insufficient result after the 6 month follow up assessment. With 61 “events”, 4 robust true predictors (15 observations per predictor variable) of non-responders can be identified and used for the risk score of non-responders [30].

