**Methods/design:**

The study consists of two parts: the first part is a randomised controlled trial with school-aged children (8–12 yrs) with AD(H)D. Two groups (each n = 50) will be randomly assigned to a well studied computerized working memory training ‘Cogmed’, or to the ‘Paying attention in class’ intervention which is an experimental school-based executive function training. Children will be selected from regular -and special education primary schools in the region of Amsterdam, the Netherlands. The second part of the study will determine which specific characteristics are related to non-response of the ‘Paying attention in class’ intervention. School-aged children (8–12 yrs) with AD(H)D will follow the experimental school-based executive function training ‘Paying attention in class’ (n = 175). Academic performance and neurocognitive functioning (primary outcomes) are assessed before, directly after and 6 months after training. Secondary outcome measures are: behaviour in class, behaviour problems and quality of life.

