
### Strengths and limitations

Our study has several strengths and limitations. Our first study is randomised and controlled, which is the strongest design to establish efficacy, and the sample size is large. Second, Green and colleagues [13] recommended that academic performance, planning, goal attainment and following rules should be assessed as outcome measures in future studies. Our study includes these recommendations by using tests that have been standardized in Dutch samples. Also we assess the quality of life of the children which hasn’t been done in earlier studies. Finally, in both conditions children receive active treatment and children that do not respond sufficiently to the experimental intervention are offered the Cogmed intervention which had already been proven effective. One limitation of this study is that the interventions from the randomised controlled trial differ on certain aspects, primarily on their content and applicability, which could make it difficult to compare the interventions in terms of efficacy. Another limitation, that has been outlined in recent reviews [34,35], is the use of single tasks to assess the generalization effects of working memory training. It is not clear whether the improved performance reflects change to an underlying ability or reflects practice of a task that strongly resembles trained tasks. Therefore we should be cautious when interpreting results on both near and far transfer effects such as attention or academic performance.

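### The 80% power claimed for the primary outcome measures as a group holds for one unadjusted comparison only, while Table 1 makes 12 measures (13 scores) primary at two post-training visits and ranks none first

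*Protocol article*

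**What the plan says.** The Abstract makes two whole domains primary: "Academic performance and neurocognitive functioning (primary outcomes) are assessed before, directly after and 6 months after training". Table 1 (Measures and procedures) then lists 12 measures under primary outcomes, from Creature counting to Comprehension of instruction. One of them, the BRIEF, a "70 item questionnaire designed to assess executive functioning in the home and school environments", is completed by both parent and teacher, which makes 13 scores. All are taken at baseline (T1), directly after treatment (T2) and six months later (T3).

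The Sample size section sets up the first study "with two trial arms, 50 children in each trial arm" and says that "an effect size of 0.60 can statistically be demonstrated (P < 0.05, 80% power) for comparison of the primary outcome measures of both interventions". The effect of 0.60 is tied to an "expected clinically relevant difference of 3 points and a standard deviation of 5 on the subtest Digit span from the WISC-III". No other measure is mentioned in support.

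The Statistical analysis section is one sentence. It plans a multivariate repeated-measures analysis of the primary and secondary outcomes. It does not say what result would count as success on the primary outcomes.

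**The concern.** Which outcomes are primary is a protocol decision, and this protocol has made it: all 12 measures are, with none ahead of the others. The power sentence speaks of the primary measures in the plural but carries the arithmetic of a single two-group comparison. A reader would take it that the trial has 80% power for its primary question, although that question is spread over 13 scores and two visits.

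Two things are at stake. If the number of primary comparisons is allowed for at analysis, the real power is well below the figure given. If it is not, a difference on any one score could be reported as a primary finding when it arose by chance.

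The choice of illustration adds to this. The Discussion ties implementation in schools to improved academic performance, but the only measure with a stated clinically relevant difference is a verbal working memory test. Both interventions train working memory, Cogmed as its core content. Under Strengths and limitations the authors accept that improvement may be one that "reflects practice of a task that strongly resembles trained tasks". A Digit span difference by itself would therefore say little about academic performance.

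**Working it through.** **Inputs.** From the Sample size section: n = 50 per arm, difference 3, SD 5, significance level 0.05, power 80%. From Table 1: 12 primary measures, 13 scores, two post-training visits, hence 13 × 2 = 26 score-by-visit comparisons if each is tested separately. Assumption: two-sided tests (sidedness is not stated).

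**Step 1: the plan's own figure.** d = 3/5 = 0.60, as stated. By the normal approximation, n per arm = 2(1.960 + 0.842)² / 0.60² = 43.6, so 44 (45 by t-test). With 50 per arm, d√(n/2) = 0.60 × 5 = 3.00 and power = Φ(3.00 − 1.96) = 85.1% (84.4% by t-test). The effect detectable with 80% power is 0.57 by t-test. The stated 80% is thus slightly conservative for one unadjusted comparison. An unstated dropout allowance of 10–12% would explain 50 rather than 44 or 45.

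**Step 2: power when several primary comparisons share the 5%.** Bonferroni level 0.05/k, two-sample t-test, n = 50 per arm:

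| Comparisons k | Level | Power at d = 0.60 | Detectable d (80% power) | n per arm for 80% at d = 0.60 |
|---|---|---|---|---|
| 1 | 0.05 | 84% | 0.57 | 45 |
| 2 | 0.025 | 76% | 0.62 | 55 |
| 12 | 0.00417 | 53% | 0.76 | 79 |
| 13 | 0.00385 | 52% | 0.76 | 80 |
| 26 | 0.00192 | 43% | 0.81 | 89 |

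Two comparisons are already enough to bring power below 80%.

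**Step 3: chance findings, conditionally.** Suppose each score is tested at 0.05 and any one significant result counts as success. Under independence the risk of at least one false positive is 1 − 0.95^k: 1 − 0.95¹³ = 48.7% and 1 − 0.95²⁶ = 73.6%. The document gives no correlations, so a range was simulated with equal pairwise correlation:

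| Correlation | 13 tests | 26 tests |
|---|---|---|
| 0 | 49% | 74% |
| 0.3 | 42% | 62% |
| 0.5 | 33% | 48% |
| 0.7 | 24% | 32% |
| 0.8 | 19% | 24% |
| 0.9 | 14% | 17% |

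A more realistic structure for 26 tests (correlation 0.3–0.5 between measures, 0.5–0.8 between visits on the same measure) gives 47–63%.

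**Step 4: does the multivariate analysis restore the claim?** Take one Hotelling T² test of 13 scores at one visit, 50 per arm, level 0.05. If one score moves by 0.60 and the scores are uncorrelated, the squared distance is 0.36, the noncentrality is 25 × 0.36 = 9, and power is 39%. If all 13 move by 0.60 with pairwise correlation r, the squared distance is 0.36 × 13/(1 + 12r), and power is 90%, 70% or 54% at r = 0.3, 0.5 or 0.7. These effect patterns are assumptions. They show that 80% at an effect of 0.60 is not a property of the omnibus test, whose power depends on inputs the document does not give.

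**The case against.** The strongest reply is that nothing in the article says each measure will be tested separately at 0.05. The only stated analysis is multivariate with repeated measures. An omnibus test of that kind would hold the error rate at 5% when there is no effect on any measure, and it would not call for separate T2 and T3 tests. This stands. A reader might infer that 13 or 26 separate tests at 0.05 are planned and that the trial therefore has a false-positive risk somewhere between 24% and 74%. The document does not support that as a fact about the plan: the test count, the correlation and an any-one-wins rule would all be assumed, and 74% further requires two visits on the same test to be independent. If every primary measure had to succeed, there would be no inflation at all.

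It is also fair that multiplicity procedures are commonly left to a full protocol or SAP, neither of which is shown. Their absence from a condensed article is not the finding.

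The sample size text can be read as giving a general standardised effect, with Digit span as a worked conversion. On that reading the sentence is correct, even conservative, for each measure taken alone. It still does not cover the set of measures it names.

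Finally, the article does not say that the trained tasks resemble Digit span in particular, and it discloses the practice limitation in general terms. The Abstract and Aims also name neurocognitive functioning alongside academic performance, so a demand that the primary outcome be academic would be partly preference.

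None of this removes the mismatch. The power was not worked out for an omnibus test. Such a test would not show which outcome changed, and it would not fully protect follow-up claims on single measures when only some effects are absent.

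**Conclusion.** The point holds in a limited form. The article fixes 12 measures (13 scores) at two post-training visits as primary without ranking them, and attaches to them a power statement that is right for one unadjusted comparison only. At d = 0.60 and 50 per arm, power is about 84% for that single comparison, 76% over two Bonferroni-adjusted comparisons and 52% over 13, where the detectable effect is about 0.76. These figures assume two-sided t-tests and no loss to follow-up.

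The false-positive figures are conditional on testing each score at 0.05 and accepting any one as success. For 13 tests they are 49% under independence and 33%, 24% or 19% at correlations of 0.5, 0.7 or 0.8. They are higher if both visits are tested separately, up to 74% for 26 independent tests. They show what the wording leaves open, not what the plan commits to.

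**What to change.** Either of two changes resolves it.

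1. Name one primary outcome at one visit, or one per domain at one visit with alpha split or a fixed sequence. Make the other Table 1 measures and the other visit secondary. Restate the sample size sentence as the power for that comparison, with a difference and SD for the measure chosen, since 3 and 5 apply to Digit span only. With an equal split over two domains, 50 per arm gives 76% power at 0.60 and a detectable effect of 0.62. A fixed sequence keeps 0.05 for the first test.

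2. Keep all measures primary at one visit, apply Holm over the 13 scores, and restate the detectable effect as about 0.76. That is the Bonferroni value and so conservative for Holm. If both visits stay primary, the figure is about 0.81.

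Whether the lead measure is academic or neurocognitive is for the sponsor to decide. Given the conceded practice effect, a span task alone should not carry a conclusion about academic performance. In either case, say how the multivariate analysis relates to the primary comparison and what result counts as success.

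The cost is wording in the protocol and analysis plan, with no extra data. The downside is that most measures become secondary, or the stated detectable effect becomes less favourable.

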**Discussion:**

So far, there is limited but promising evidence that working memory – and other executive function interventions can improve academic performance. Little is know about the applicability and generalization effects of these interventions in a classroom situation. This study will contribute to this lack of information, especially information related to real classroom and academic situations. By taking into account the costs of both interventions, level of impairment and individual characteristics of the child (stepped-care approach) we will be able to address treatment more adequately for each individual in the future. Trial registration: Nederlands Trial Register NTR3415.

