
### Aims

(1) The aim of the first study is to examine the effects of a working memory – and executive function training on academic performance, neurocognitive functioning, behaviour in class, behaviour problems and quality of life of children with AD(H)D between the age of 8 and 12 years.

(2) The aim of the second study is to investigate which specific characteristics are related to non-response of the ‘Paying attention in class’ intervention. By offering Cogmed to the non-responders, we will obtain insight into the effectiveness of both interventions, taking into account individual characteristics, the level of impairment and the costs (stepped-care approach).

With the result of both studies we hope to obtain more insight in the effective elements of both interventions so that treatment can be more individually tailored in the future.

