### Design

The first study is a randomised controlled trial in which children will be randomly assigned to the Cogmed RM [10] intervention (n=50) or the experimental ‘Paying attention in class’ intervention (n=50). We expect that for some children treatment can not be started immediately after enrollment. They will be placed on a waiting list. An extra measurement of academic performance and neurocognitive functioning (primary outcomes) will be administered for the children on the waiting list, this will be a control group (n=50). The second study partially replicates and also extends the first study. This second study investigates which specific characteristics are related to a non-response of the ‘Paying attention in class’ intervention, which requires 175 children including the 50 children from the first study. Based on ethical considerations, Cogmed RM [10] will be offered to the non-responders of the ‘Paying attention in class’ intervention after the follow up assessment (6 months).

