#### Paying attention in class

‘Paying attention in class’ is an experimental executive function training that has been developed by our research team. The child is trained individually for 5 weeks, 5 times a week, approximately 45 minutes a day; the same duration as in the Cogmed protocol. This ‘Paying attention in class’ has three aims. First of all, the most important aim of this intervention is to offer psycho education about executive functions that are related to classroom behaviour. By making children more aware of these executive functions needed for adequate classroom behaviours, they obtain more insight in their own learning behaviour. The psycho education addresses five executive functions that are important in a learning situation, namely: paying attention, planning skills, working memory, goal-directed behaviour and metacognition. It will be offered through a MP3 player, based on a ‘brain castle’ theme in which specific compensatory strategies and pitfalls are explained to the child. Every session starts with psycho education that is related to one of the above mentioned executive functions. After hearing this, the child is asked to make a neuropsychological - and school task related exercise in which the psycho education has to be applied. The second aim of this intervention is to train working memory functions. This is done by three adaptive working memory tasks: one visual-, one verbal-, and one instruction paradigm task (30 trials in total). The child will be encouraged to use the compensatory memory-strategies from the psycho education. The third and final aim of this intervention is to make a transfer to a classroom-situation, this will be achieved through several ways. First of all, the strategies introduced through the psycho education as described above will be illustrated and practiced by performing school related tasks. Second, the child brings a registration card to class that reminds him/her of the practiced skill of the day (for example, ‘I repeat what is said’). This card includes the name of the specific compensatory strategy. By using a registration card, the child will be reminded what to practice in the classroom. Also it will inform the teacher about the specific executive function and strategy that is practiced on that day so that he/she can reward the child for applying it in class. Finally, to optimize the transfer from the training session to a situation in class we closely involve the teacher in the process by informing him/her with the protocol and by giving him/her an active part in the process. The teacher will receive psycho education about the use of executive functions in the classroom through a written manual, which will increase their knowledge how to recognize and stimulate such behaviour in learning situations. The teacher also receives structured observation forms daily in which he/she can record whether the child applies the practiced strategies in class. The ‘Paying attention in class’ intervention is experimental, so the exact costs are unknown, but we are aiming at a price of €25 a workbook. The costs of a ‘Paying attention in class’ training will be equal to that of the Cogmed Coach Training but there will not be a monthly license fee.

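### Study 2 trains every child the same way, so it can give a prognostic score for poor result after that training, but cannot by itself show the effectiveness of both trainings or which child should get which

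*Protocol article*

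**What the plan says.** The Design section describes Study 2 as one group given *Paying attention in class*, "which requires 175 children including the 50 children from the first study". The Sample size section states "We expect that 35% (n = 61) of the 175 included children" "will show no or insufficient result after the 6 month follow up assessment", and allows four predictors for the risk score at 15 events each. The article does not say on which outcome, cut-off or metric non-response is judged.

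T3 is 6 months after a 5-week training (Table 1; Interventions). Under Design, Cogmed is offered to the non-responders after T3. Table 1 lists no later assessment.

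Three uses of the results are named:
- Aim 2 first asks which characteristics are related to non-response. It then says that giving Cogmed to non-responders will yield insight into the effectiveness of both interventions. The Discussion repeats this for Study 2.
- The Aims close with the hope of learning from both studies "so that treatment can be more individually tailored in the future".
- The Abstract says of the whole project that "we will be able to address treatment more adequately for each individual in the future".

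**The concern.** A trait that goes with poor result in a single trained group may mark one of three things: a child who would have progressed little anyway, a baseline score that was high by chance, or a child whom this training does not help. Only the third bears on the choice of training, and one arm cannot separate it from the other two. Over about 7 months, children of 8 to 12 change through schooling, maturation and repeated testing. The medication criterion under Inclusion covers stability only up to the end of training.

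The Cogmed step does not repair this. Children selected for a poor result at T3 would be expected to move back towards the average whatever they receive next, and no concurrent group shows how much.

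At stake is the stepped-care conclusion. A score that looks convincing could be read as a reason to prefer one training for a child when it carries no such information.

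**Working it through.** **The plan's own figures.** 175 × 0.35 = 61.25, so 61 events. 61 / 15 = 4.07, so four predictors. Both reproduce. From T1 to T3 is 5 weeks (1.15 months) + 6 months = 7.15 months.

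**Regression to the mean, no training effect.** Assumptions not in the article: standard normal scores at T1 and T3 with test-retest correlation r, and non-response = lowest 35% of T3 − T1. The correlation of baseline with change is then −√((1 − r)/2). In 1,000 simulated studies of 175 children per value of r, with logistic regression on baseline score:

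| r | correlation of baseline with change | AUC of baseline score | odds ratio of non-response per SD | studies with p < 0.05 |
|---|---|---|---|---|
| 0.6 | −0.45 | 0.71 | 2.3 | 100% |
| 0.7 | −0.39 | 0.68 | 2.1 | 98% |
| 0.8 | −0.32 | 0.64 | 1.7 | 92% |
| 0.9 | −0.22 | 0.60 | 1.5 | 64% |

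At r = 0.7, in 400,000 simulated children, apparent non-response is 20% in the lowest baseline third and about 52% in the highest.

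**If non-response means a low level at T3 instead.** With the same null and the lowest 35% of T3 scores, the AUC of baseline is 0.78 (r = 0.6) to 0.94 (r = 0.9), in the opposite direction. At r = 0.7, non-response is 68% in the lowest third and 7% in the highest. The definition sets the direction of the association. It does not remove it.

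**Natural course.** A trait correlated 0.2, 0.3 or 0.4 (assumed) with untreated change, and unrelated to any training effect, has p < 0.05 in 54%, 88% and 99% of simulated studies of 175.

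**With a concurrent arm.** Under the same null, the baseline-by-arm interaction with 50 v 50 has p < 0.05 in 4.7% (r = 0.6) and 4.4% (r = 0.8) of runs, close to nominal. The detectable difference in slopes at 80% power, two-sided 0.05, is (1.960 + 0.842) × √(1/50 + 1/50) = 0.56 SD of change per SD of the trait.

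**Overlap between building and testing.** The 50 randomised children given *Paying attention in class* are among the 175, and the 50 randomised to Cogmed are not. A score built on all 175 is therefore overfitted in one arm only. With pure-noise predictors and a four-predictor score, the interaction had p < 0.05 in about 8% of runs with no selection, and in 12% and 16% with selection from 10 and 20 candidates (numbers assumed). With those 50 left out of the building step it was about 4 to 6%.

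**The case against.** Much of the case on the other side stands.

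- *Non-response is not defined as change from baseline.* Correct. The phrase in the Sample size section leaves the metric open and the full protocol may settle it. The table above illustrates one definition and does not describe this plan. The argument against a comparative reading does not depend on it.
- *Aim 2 is answerable.* A reader might infer that the aim fails altogether. It does not: which characteristics go with non-response is a prognostic question that one trained cohort can address.
- *Children are not steered by the score.* A reader might infer that the score assigns children to trainings. The article says nothing of the kind. Cogmed is offered to observed non-responders on ethical grounds, and the tailoring sentence is a hope resting on both studies, including the randomised one.
- *Growth may be handled.* Tests were chosen partly for Dutch norms (Measures and procedures). Norms can remove average growth, but not regression to the mean or differences between children in natural course.
- *There is a waiting-list control group of 50.* It is not randomised, adds one measurement before training, and has no described untreated follow-up to T3.
- *A moderator analysis may be planned elsewhere.* It may, and its absence from a short statistics section is not the point. The article itself attributes comparative insight to the one-arm study.
- *The AUCs are modest and concern one variable.* True. Baseline score is not named as a candidate predictor, and not every trait will be affected.

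**Conclusion.** The point holds as a mismatch between design and claim. Study 2 can yield a prognostic score for poor result after *Paying attention in class*. By itself it cannot show the effectiveness of both interventions or which child should get which training.

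The size is illustrative: AUC 0.71 to 0.60 for baseline score with no training effect, under an assumed test-retest correlation of 0.6 to 0.9 and an assumed definition of non-response as the lowest 35% of change. The 61 events and four predictors are arithmetically right, and the randomised comparison in Study 1 is unaffected. The change is worth making before results are interpreted, since it decides what may be concluded about stepped care.

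**What to change.** 1. Describe the product of Study 2 as a prognostic score for poor result after this training. Remove the statements that Study 2 gives insight into the effectiveness of both interventions or supports the choice between them, unless step 3 supports them.
2. For the score, judge response on age- or grade-normed values, which the choice of tests with Dutch norms appears to allow for most tests, and account for baseline score and age. This concerns the analysis only, not who is offered Cogmed. If these two count among the four predictors that 61 events allow, two places remain for other traits.
3. In the 100 randomised children, estimate the trait- or score-by-arm interaction at T3 with its confidence interval. Use a score built only on the 125 non-randomised children, or a cross-fitted one, so that no child's own outcome enters that child's score.

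The cost is wording and one further analysis of data already planned, with no new visits or recruitment. There are three downsides. The claim becomes more modest. A score built on 125 children has about 125 × 0.35 = 44 events, which at the plan's 15 per predictor carries only two predictors (44 / 15 = 2.9); cross-fitting uses more of the data. The interaction will be imprecise, with only about 0.56 SD of change per SD of the trait detectable at 80% power, so an interval that includes zero should not be read as evidence that the trainings suit all children equally.
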